### Recruitment and participants

The study will be conducted in first grade classrooms with children aged 5–6 years in three education regions in Queensland, Australia: Brisbane (Metropolitan Region, urban schools), Gold Coast (South East Region, urban schools), and Townsville (North Queensland Region, rural schools). Eightschools in each region will be randomly selected to participate. Trained research assistants not involved in data collection will initially contact schools. An information sheet detailing the *Learn to be safe with Emmy and friends*™ program and explaining the evaluation will be sent to school principals who will be asked to provide consent for their school’s participation. Randomisation will be conducted following principal consent, after which time, schools will be asked to distribute standardised information sheets with consent forms (either waitlist-control or intervention version) to parents/guardians (hereafter, parents) of all children enrolled in first grade. Parents return consent forms to the school if they agree for their child to participate.

A simple random sampling strategy with individuals as the primary sampling unit was assumed, and G*Power was then used to estimate sample size. This returned a suggested total sample size of at least 100 children per group at each of three sites. Based on similar studies [22] that have used cluster sampling with schools as the primary sampling unit, the sample size with this design effect was estimated to be approximately 1.5, taking into account potential attrition of (20 %) owing to student absences and/or mobility. In addition, enough power will be needed to examine the effects for subgroups (sex/school/family/stress, etc.). Therefore, a total sample size of at least 1350 is required in this study to test the effectiveness of the intervention. Assuming conservative class sizes of 20 students per class (60 children per school; 9 schools in each region), a final initial sample size of 1620 Year 1 children and their parents is planned to give sufficient power for this study.

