## Methods/Design

The Human Research Ethics Committees at Griffith University (GU Ref No: PSY/48/14/HREC) approved this study, as did the Research Committee at the Department of Education and Training, Queensland. It is also registered with the Australian and New Zealand Clinical Trials Register (ACTRN12615000917538) and has received Australian Research Council funding under the Linkage Projects scheme (ID: LP130100304) in a partnership between Griffith University, James Cook University, Queensland University of Technology and the not-for-profit organisation, Act for Kids.

The study consists of a three-site cluster randomised control trial using a waitlist-control group. The unit of randomisation will be the school. The unit of analysis will be individual children; however the nesting effects of classes, schools, and site location will be taken into account through hierarchical modelling. Data from parents/guardians about immediate child outcomes will be paired with the respective child data. The main outcome evaluation will be supplemented by a process evaluation using fidelity data from facilitators, session auditors, and satisfaction surveys completed by parents/guardians and teachers.

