### Randomisation

After school recruitment and principal consent, a concealed randomisation process will be undertaken using a computer-generated list of random numbers. Entire schools will be randomised to intervention or control to prevent knowledge and skill sharing among students across conditions. Researchers conducting data collection and data analysis will be blinded to group membership.

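### Parents consent after their school is randomised, on a form that differs by arm, so families can self-select differently in the two arms; the exposure is greatest for the in-vivo test, which has no baseline

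*Protocol article*

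**What the plan says.** The order of events is set out in the protocol article under Recruitment and participants. "Randomisation will be conducted following principal consent", and parents are approached only after that: "schools will be asked to distribute standardised information sheets with consent forms (either waitlist-control or intervention version"). The forms go to the parents of every first-grade child. Entry is by opting in: "Parents return consent forms to the school if they agree for their child to participate".

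Methods/Design separates the two units: "The unit of randomisation will be the school" and "The unit of analysis will be individual children".

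The Randomisation section describes a concealed process carried out after school recruitment and principal consent, and states that "Researchers conducting data collection and data analysis will be blinded to group membership". Planned analyses adds intent-to-treat analyses directed at differential drop-out, and hierarchical modelling for classroom and school effects.

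**The concern.** Randomising schools makes the two sets of schools comparable, and with them the full first-grade intakes. It does not by itself make the children who are analysed comparable, because they are a subset formed after allocation. Here parents form that subset, and they decide on papers that differ by arm. What the arms are offered differs too: one has the program at once and assessments to 18 months, while the other has assessments to six months and the program afterwards (Control group; Assessment procedures T1-T5). That could move consent in either direction.

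If consent differs by arm in a way related to the outcome, for example through family engagement or safety teaching at home, part of the observed arm difference reflects who consented and not the program. None of the stated safeguards addresses this:

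- Concealment protects the school allocation, which is already made when parents are approached.
- Blinding covers data collectors and analysts, not parents or schools.
- Intent-to-treat for drop-out acts only after enrolment.
- Hierarchical modelling deals with correlation within schools, not with selection.

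**Working it through.** **No stated figure to reproduce.** The article gives no consent rate, overall or by arm, and no effect size, significance level or power. The order of events comes from the text. Everything about size below is assumption.

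**Step 1: which outcomes are exposed.** Let s1 and s0 be the shifts in mean level caused by selective consent in the intervention and waitlist arms, and τ the true effect.

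- *No baseline.* The Observed Protective Behaviours Test (OPBT) is given only at post-test or six months, and Planned analyses compares it by t-test at T2 and T3. The expected arm difference is τ + (s1 − s0), so the whole selection shift enters the estimate. This is hypothesis 3, and the abstract counts use of skills in the simulated situation among the primary outcomes.
- *Change from T1.* Hypothesis 1 compares changes from pre-test to post-test, and the mixed ANOVAs test Group by Time. If the shift is the same at T1 and afterwards, the expected difference in change is [τ + (s1 − s0)] − (s1 − s0) = τ. The shift cancels whether or not its cause was measured. If only a fraction k of it is still present later, the remaining bias is (k − 1)(s1 − s0). What can survive is selection related to response to the program, ceiling effects or regression to the mean.
- *Parent checklist (hypothesis 2).* Intervention families receive program materials at home and complete a weekly discussion monitor, so they know their arm by post-test whatever the consent form says. Only the baseline rating can be protected.

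**Step 2: illustrative size for an outcome without a baseline.** Suppose consent is p1 in one arm and p0 in the other (p1 > p0), that those who would consent at the lower rate would also consent at the higher, and that the extra consenters differ from them by δ SD. Then shift = [(p1 − p0)/p1] × δ.

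| Consent (assumed) | δ = 0.2 | δ = 0.5 |
|---|---|---|
| 70% vs 60% | (0.10/0.70) × 0.2 = 0.03 SD | (0.10/0.70) × 0.5 = 0.07 SD |
| 70% vs 50% | (0.20/0.70) × 0.2 = 0.06 SD | (0.20/0.70) × 0.5 = 0.14 SD |

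**Step 3: a second model as a check.** Let willingness to consent have correlation ρ with the outcome and let families consent above a threshold. Then bias = ρ × [λ(c1) − λ(c0)], where λ(c) is the inverse Mills ratio at consent rate c. The false rejection rate is for a two-sided 5% z-test with 720 children invited per arm (12 schools × 60, using eight schools in each of three regions) and a design effect of 1.5.

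| Consent (assumed) | ρ (assumed) | Bias, absolute SD | False rejection |
|---|---|---|---|
| 70% vs 70% | any | 0 | 5% |
| 70% vs 60% | 0.1 | 0.015 | 5.4% |
| 70% vs 60% | 0.3 | 0.04 | 8.5% |
| 70% vs 50% | 0.3 | 0.09 | 19% |
| 80% vs 50% | 0.5 | 0.22 | 78% |

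The two models agree in order of magnitude, and the last row is a deliberately extreme corner. The rejection rates assume that every consenting child contributes to one comparison. If the OPBT is split between T2 and T3, each test has fewer children and the excess rejection is smaller, but the bias in SD is unchanged.

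**The case against.** The strongest reply is that most of the child outcomes are analysed as change, and a stable difference between the families who consent in each arm drops out of a Group by Time test. That stands. A reader might infer from the sequence that every between-arm comparison is biased by the amounts in the tables. The documents do not support this: the amounts apply directly only to outcomes without a baseline.

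The forms are also standardised and go to every first-grade family, so nobody who knows the arm picks which families to approach. That stands too, and it narrows the risk to parents' own choice.

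The content of the forms is not shown. That they disclose the arm is inferred from there being a version named for each arm; the inference is strong, but it is an inference. It is equally tempting to say that consenting means receiving the program now in one arm and waiting in the other. The article does not say whether a child without consent misses the classroom sessions or only the assessments. If consent covers assessment alone, the motive to opt in differs less between arms.

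Finally, a reader might conclude that a neutral form would keep the parent checklist free of knowledge of the arm. It would not, because intervention parents learn the arm during the program.

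What the reply leaves standing is the sequence itself, the two versions of the form, the OPBT, and the absence of a stated safeguard against selective consent.

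**Conclusion.** The point holds as a design risk. Children are enrolled after allocation, by parents who receive different papers in each arm, and nothing described in the article protects against differing consent. It is not evidence that the arms will be unbalanced: a reader might infer actual imbalance, but the document supports only the possibility, with size and direction unknown.

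The exposure is direct for the OPBT, limited for outcomes tested as change from T1, and confined to the baseline rating for the parent checklist. The figures (0.03 to 0.07 SD at 70% versus 60% consent, 0.06 to 0.14 SD at 70% versus 50%) rest wholly on assumed consent rates and assumed differences between families. Identical consent in both arms, in rate and in kind of family, gives no bias. The case for acting is that selection at enrolment cannot be undone afterwards, while preventing it costs little.

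**What to change.** Use one arm-neutral information sheet and consent form in all schools, stating that the program will come either now or after the six-month assessment. Close parental consent before the allocation is released to the school. Compare consent rates and baseline characteristics by arm.

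Completing T1 before release would also protect the baseline parent rating and the child baseline, but T1 falls only one week before the program starts, so this is desirable only if that schedule allows it.

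The cost is an ethics amendment to replace two forms with one, and shorter notice for scheduling facilitators. The change does not keep intervention parents unaware of their arm at post-test, so parent-reported change stays open to that influence.

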**Methods/Design:**

A three-site cluster randomised controlled trial (RCT) of Learn to be safe with Emmy and friends™ will be conducted with children in approximately 72 first grade classrooms in 24 Queensland primary (elementary) schools from three state regions, over a period of 2 years. Entire schools will be randomised, using a computer generated list of random numbers, to intervention and wait-list control conditions, to prevent contamination effects across students and classes. Data will be collected at baseline (pre-assessment), immediately after the intervention (post-assessment), and at 6-, 12-, and 18-months (follow-up assessments). Outcome assessors will be blinded to group membership. Primary outcomes assessed are children’s knowledge of program concepts; intentions to use program knowledge, skills, and help-seeking strategies; actual use of program material in a simulated situation; and anxiety arising from program participation. Secondary outcomes include a parent discussion monitor, parent observations of their children’s use of program materials, satisfaction with the program, and parental stress. A process evaluation will be conducted concurrently to assess program performance.

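### The planned 1620 children assumes 27 schools where the design has 24 (at most 1440), and the required 1350 does not follow from the stated inputs

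*Protocol article*

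**What the plan says.** All of the sizing is in the protocol article, Methods/Design, Recruitment and participants, apart from the abstract's count of schools.

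- **Number of schools.** The abstract plans for "approximately 72 first grade classrooms in 24 Queensland primary (elementary) schools". The recruitment text agrees: "Eightschools in each region will be randomly selected to participate", in three regions.
- **Base size.** The calculation begins without clustering: "A simple random sampling strategy with individuals as the primary sampling unit was assumed". Its result: "This returned a suggested total sample size of at least 100 children per group at each of three sites".
- **Inflation.** Citing similar studies that sampled schools, the article says "the sample size with this design effect was estimated to be approximately 1.5, taking into account potential attrition", with attrition put at 20%. It then says that subgroup analyses also need power, without a figure, and concludes that at least 1350 children are required.
- **Planned total.** Classes of 20 are assumed, and the total follows from "60 children per school; 9 schools in each region), a final initial sample size of 1620 Year 1 children and their parents is planned". This is said to give the study sufficient power.
- **Participation.** Consent is active: "Parents return consent forms to the school if they agree for their child to participate". No participation rate enters the calculation.

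**The concern.** A sample-size statement should lead from its inputs to its total, and the total should fit the design. Here neither holds. The planned total uses a number of schools that differs from the number given in the same section and in the abstract. The required minimum cannot be reached from the inputs shown. One factor is asked to cover two different things, clustering and attrition, so a reader cannot tell how much of it allows for randomising whole schools.

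At stake is the claim of sufficient power, which the article makes after naming subgroup effects as one of its needs. In a school-randomised trial, precision depends mainly on the number of schools and the ICC. A total that presumes three schools more than the design has, with an unclear clustering allowance, does not tell the reader which effects the trial can detect.

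**Working it through.** **1. The planned total.**
- As written: 3 regions x 9 schools x 60 = 27 x 60 = 1620. The figure is reproduced exactly.
- For the stated design: 3 x 8 x 60 = 24 x 60 = 1440, and 72 classes x 20 = 1440.
- Difference: 1620 - 1440 = 180, and 180/1620 = 11.1%.

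**2. The required 1350.**
- Base: 100 per group x 2 groups x 3 sites = 600.
- With the stated factor: 600 x 1.5 = 900.
- With 20% attrition added: 900 x 1.2 = 1080, or 900/0.8 = 1125. Neither is 1350.
- 1350/900 = 1.5, so 1350 = 600 x 1.5 x 1.5 = 600 x 2.25. The second 1.5 is not stated. From its place in the text it appears to be the subgroup allowance.
- 1620/1350 = 1.2, so attrition may have been added at this last step. Division by 0.8 would give 1350/0.8 = 1687.5, or 1688.

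**3. What the 1.5 leaves for clustering**, from design effect DE = 1 + (m - 1) x ICC with m = 60.

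| Reading of the 1.5 | DE | ICC = (DE - 1)/59 |
|---|---|---|
| Includes 20% loss, removed as x 0.8 | 1.20 | 0.0034 |
| Includes 20% loss, removed as / 1.2 | 1.25 | 0.0042 |
| All clustering | 1.50 | 0.0085 |

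This concerns the factor alone. The total inflation is larger: 1350/600 = 2.25, 1440/600 = 2.4 and 1620/600 = 2.7.

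**4. Participation with 24 schools.** Enrolling 1350 needs 1350/1440 = 93.75%. At assumed rates of 80% and 60% the trial enrols 1152 and 864.

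**5. What 24 schools can support**, at full participation and 20% loss.
- Analysed: 1440 x 0.8 = 1152, or 48 per school and 12 x 48 = 576 per arm.
- These equal 600 independent children when 1152/(1 + 47 x ICC) = 600, so ICC = (1152/600 - 1)/47 = 0.0196.
- Detectable difference at 80% power, two-sided 5%, with 24 - 2 = 22 degrees of freedom and no baseline adjustment: (t0.975 + t0.80) x sqrt(2 x DE/576) = (2.074 + 0.858) x sqrt(2 x DE/576).
- The article gives no ICC, so the range below is assumed.

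| Assumed ICC | DE = 1 + 47 x ICC | Effective children | Detectable effect (SD) |
|---|---|---|---|
| 0.01 | 1.47 | 784 | 0.21 |
| 0.02 | 1.94 | 594 | 0.24 |
| 0.05 | 3.35 | 344 | 0.32 |
| 0.10 | 5.70 | 202 | 0.41 |

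For comparison, 600 independent children (300 per arm) give (1.960 + 0.842) x sqrt(2/300) = 0.23 SD.

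**The case against.** The strongest reply is that the planned sample is larger than the 1.5 suggests. A reader might infer from the implied ICC of 0.003 to 0.004 that clustering is hardly provided for. The document does not support that. The figure describes the 1.5 read literally and alone; 1440 is 2.4 times the base and, after 20% loss, still yields 600 effective children up to an ICC of about 0.02. If a single pooled comparison of 100 per group were enough, the limit would be (1152/200 - 1)/47, about 0.10. With no ICC given, the cluster size of 60 cannot contradict the design effect, so a clustering shortfall is possible but not shown. This part of the objection stands.

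Four further points deserve weight.

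- **Where attrition sits.** If it is inside the 1.5, then 1350 is an enrolment target and 1440 exceeds it at full participation. If 1350 means children analysed, neither 1440 (1152 after loss) nor 1620 (1296 after loss) reaches it. The text does not settle this, so a shortfall against 1350 after loss is conditional.
- **Class size.** The article calls its 20 per class conservative, which may already allow something for non-participation. It does not say so, and the need for about 94% participation assumes that 20 is the full class.
- **Baseline data.** The planned analyses use repeated measures, which can lower the detectable effects above.
- **Power per site.** A reader might take the per-site base as a claim of power at each site. The article makes none; it speaks of the study as a whole and plans no analysis by site.

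A condensed article may also leave its ICC and G*Power inputs to the full protocol, so their absence is not the complaint. That does not excuse two different numbers of schools in one section, or a minimum that its printed factors do not produce.

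**Conclusion.** The point holds as a contradiction and an arithmetic gap in the sizing. Two parts need no outside assumption: 1620 belongs to 27 schools while the design has 24, which give at most 1440 (180 or 11% fewer); and the stated inputs lead to 900, not 1350, with a factor of 1.5 unexplained. The merging of attrition with the design effect is also plain in the text, but what it leaves for clustering depends on the reading.

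The consequence for power is conditional. At full participation and 20% loss, 24 schools match the article's own base if the ICC is at or below about 0.02 and fall short of it above that. Across the assumed ICCs of 0.01 to 0.10 the detectable effect runs from about 0.21 to 0.41 SD without baseline adjustment, against 0.23 SD for 600 independent children. At an ICC of 0.02 the loss is negligible (0.24 SD). The documents therefore do not show that the trial is underpowered. They show that its statement of sufficient power rests on figures that do not agree with the design or with each other.

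**What to change.** 1. Reconcile the number of schools across the abstract, the recruitment text and the sample-size sentence, and restate the planned total for it. With 24 schools this is 1440 x the expected participation rate, in place of 1620.
2. Set out the steps from the base of 600 as separate factors: design effect 1 + (m - 1) x ICC over a stated ICC range, with m the expected number analysed per school; attrition by division by 0.8; and the subgroup allowance with its size and reason. Say whether the required minimum counts children enrolled or analysed.
3. Report the detectable effect that results, with or without baseline adjustment as planned, and limit the statement of sufficient power, including for subgroups, to what that size supports.

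The cost is a rewritten paragraph and one small table. No extra schools are needed and the design does not change; the stated sample size becomes less favourable.

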### Inclusion/exclusion criteria

Children will be eligible to participate in the study if they are enrolled in a first grade classroom at a participating school. Schools who have taught an alternative child protection education program to their first grade students will be ineligible to participant in this RCT.

### Randomisation

After school recruitment and principal consent, a concealed randomisation process will be undertaken using a computer-generated list of random numbers. Entire schools will be randomised to intervention or control to prevent knowledge and skill sharing among students across conditions. Researchers conducting data collection and data analysis will be blinded to group membership.

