### Planned analyses

Mixed factorial analyses of variance (ANOVAs) will be used to examine the effectiveness of the program for primary outcomes. Analyses will be conducted to assess differences between the intervention and waitlist control conditions over time using 2 (Group: intervention, waitlist-control) x 3 (Time: T1, T2, T3) mixed ANOVAs. Primary or target outcomes include children’s knowledge of program concepts, intentions to use program knowledge, skills, and help-seeking strategies, and anxiety as a result of program participation. T-tests will be conducted to examine the difference between groups in use of program skills and disclosure during the simulated situation conducted at T2 and T3.

Following the 6-month follow-up of the children who received the program, data will be analysed to assess stability of improvement in the treatment group from post to, 6-, 12- and 18-month follow-up. One-way ANOVAs will also be conducted for these variables for the intervention group across the five time points (T1, T2, T3 and T4, T5).

Hierarchical linear modelling [37] will be used to examine any effects of the hierarchical structure of the study design. If there are hierarchical effects, this analysis will be used to account for influences of classroom (level 2) and school level effects (level 3), while examining the effects of condition (Emmy/waitlist) and within student changes over time. Regression will be used to test the mediation analyses and to examine any effects of moderators (e.g. demographic variables, parental stress, dose–response) to determine which factors may differentiate intervention effects. Intent-to-treat analyses will also be conducted to account for potential effects of differential drop-out.

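### The article mentions no stratification of school allocation by region, although the sample size is set per group per site, and the analyses it names do not carry through the promised adjustment for site

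*Protocol article*

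**What the plan says.** On allocation, the opening of Methods/Design states: "The unit of randomisation will be the school". The Randomisation section says that "a concealed randomisation process will be undertaken using a computer-generated list of random numbers", and the Abstract repeats this: "Entire schools will be randomised, using a computer generated list of random numbers". Neither place mentions region, strata, blocks or an allocation ratio. Neither says that allocation is unrestricted.

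On the regions, Recruitment and participants names three: Brisbane and Gold Coast, both urban, and Townsville, the only rural one. It says "Eightschools in each region will be randomly selected to participate", which agrees with the Abstract ("approximately 72 first grade classrooms in 24 Queensland primary (elementary) schools from three state regions"). The sample-size paragraph of the same section uses 9 schools per region, with 60 children per school. The base sample size is "at least 100 children per group at each of three sites", to which a design effect of about 1.5 and 20% attrition are applied.

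On analysis, the opening of Methods/Design says that nesting within classes, schools and site location will be handled by hierarchical modelling. Planned analyses then gives 2 (group) by 3 (time) mixed ANOVAs for the primary outcomes and t-tests for the simulated situation. A hierarchical model follows if hierarchical effects are found, and the levels it names are "influences of classroom (level 2) and school level effects (level 3"). Site does not appear there.

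**The concern.** Region is known before allocation, does not change, and by the article's own description separates urban from rural schools. With about 24 units, a list that ignores region can place noticeably more rural schools in one arm. It can also leave an arm in one region with too few schools to give the number the trial was sized on.

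Two things are at stake. The first is delivery of the per-group, per-site numbers, which no later modelling can restore. The second is chance confounding of arm with region, which a region term would handle but the analyses named for the primary outcomes and the simulated situation do not contain.

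**Working it through.** **Inputs from the article.** 3 regions; 8 schools per region (9 in the sample-size paragraph); 60 children per school; 20% attrition; base of 100 children per group per site.

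**Assumptions.** The allocation ratio is not stated, so 1:1 is assumed. Two forms of unrestricted list are shown: independent draws with probability 0.5, and a list fixed at 12:12 overall.

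**The plan's own figures.** The article gives no figure for regional balance. Its size arithmetic starts from 100 × 2 × 3 = 600. The planned 1620 is 27 × 60, whereas 24 schools give 24 × 60 = 1440. The required 1350 is not reproduced by 600 × 1.5 = 900 with 20% attrition (900 / 0.8 = 1125, or 900 × 1.2 = 1080). That is a separate point, and the conclusion here does not rest on 1350.

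**Balance with 8 schools per region, independent draws.**
- Exactly 4:4 in one region: C(8,4) / 2^8 = 70/256 = 27.3%. In all three: 0.273^3 = 2.0%.
- 6:2 or worse in one region: 2 × (1 + 8 + 28) / 256 = 74/256 = 28.9%. In at least one: 1 − 0.711^3 = 64.1%.
- 5:3 or better in one region: 1 − 0.289 = 71.1%.

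**Balance with 12:12 fixed overall.** The probability of a, b and c intervention schools is C(8,a) C(8,b) C(8,c) / C(24,12), with a + b + c = 12.
- 4:4 in all three: 70^3 / 2,704,156 = 12.7%.
- By enumeration, 6:2 or worse: 19.3% per region and 38.6% in at least one region.
- 5:3 or better in one region: 80.7%.

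**Cost in precision (equal school variances assumed).**
- Within the affected region, 6:2 against 4:4: (1/2 + 1/6) / (1/4 + 1/4) = 0.667 / 0.5 = 1.33, so 33% more variance. For 5:3, relative efficiency is 15/16 = 94%.
- Pooled and adjusted for region, information is the sum of n1 × n2 / n. With 4:4 throughout it is 2 + 2 + 2 = 6; with one region at 6:2 it is 1.5 + 2 + 2 = 5.5. The variance ratio is 6 / 5.5 = 1.09, about 9% more.

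**Cost in numbers.** Two schools enrol 2 × 60 = 120 children and retain 120 × 0.8 = 96, below 100 before any design effect. Three schools retain 144. On retained children, the 100 therefore needs 3 schools per arm. That is missed in at least one region in 64.1% of trials (38.6% with 12:12 fixed).

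**Confounding, as an illustration.** Suppose Townsville is 6:2 and the other regions 4:4. Rural schools are then 6/14 = 43% of one arm and 2/10 = 20% of the other. A comparison without a region term is shifted by 0.23 times the rural-urban difference in the quantity compared. The article gives no figure for that difference, so the shift cannot be sized further.

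**Nine schools per region.** A stratified 5:4 split gives 20/9 = 2.22 against an ideal 4.5 × 4.5 / 9 = 2.25, a loss of about 1%.

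**The case against.** The strongest objection is that the premise rests on silence. A random-number list can be drawn within region, and the article condenses a fuller protocol that may say so. Fixed recruitment per region and sizing per site fit within-region allocation. This stands: a reader might infer that simple randomisation is stated, and it is not. Every probability above is conditional on an unrestricted list.

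A reader might also infer that regional imbalance would go wholly unadjusted. The opening of Methods/Design contradicts that, since it promises to account for site location. What remains is narrower: Planned analyses does not carry the promise out.

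A third tempting reading is that acceptable balance will usually fail. That is true only of exact equality. In a single region 5:3 or better is the usual result (71% to 81%) and costs about 6% efficiency. The 33% applies to one region's own contrast, whereas the planned comparison is pooled, where one 6:2 region costs about 9%. On enrolled rather than retained children, two schools give 120 and the bare 100 is met in 93% of regions.

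Nor do 9 schools per region defeat stratification, since 5:4 is nearly fully efficient. Finally, unstratified cluster randomisation is valid and unbiased in expectation, so this is a better design choice and not the repair of an invalid one.

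**Conclusion.** The point holds in a conditional form and should be addressed. The article sizes the trial per group per site but describes an allocation method that, as written, does not secure those numbers. If the list is unrestricted and 1:1, a split of 6:2 or worse in at least one region is likely with independent draws (64%) and common with 12:12 forced (39%). The consequence is moderate: 33% more variance in that region, about 9% in the pooled region-adjusted comparison, and about 96 retained children in one arm against a stated 100.

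The analysis part does not depend on how the list was drawn. The general statement on site location and the Planned analyses section disagree, and under the ANOVAs and t-tests any chance confounding with region would go unadjusted.

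The figures assume 8 schools per region, 60 children per school, 20% attrition spread evenly, and equal school variances. How strongly region predicts the outcomes is not given.

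**What to change.** - State whether allocation is stratified by region. If it already is, one clause settles the allocation part.
- If it is not, generate the list separately within each region with equal or near-equal numbers per arm: 4:4 with 8 schools, 5:4 with 9. First reconcile the 8 and 9 in Recruitment and participants.
- Include region as a fixed effect in every arm comparison, including those now planned as mixed ANOVAs and t-tests, so that Planned analyses matches the opening of Methods/Design.

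The cost is a different list, one model term, and consenting all of a region's schools before allocating them (or using blocks within region if consent is staggered). The list must be settled before allocation, because missing schools in an arm cannot be recovered afterwards.
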